## Abstract

**Background:**

Radiotherapy (RT) is an important treatment modality for patients with brain malignancies. Traditionally, computed tomography (CT) images are used for RT treatment planning whereas magnetic resonance imaging (MRI) images are used for tumor delineation. Therefore, MRI and CT need to be registered, which is an error prone process. The purpose of this clinical study is to investigate the clinical feasibility of a deep learning-based MRI-only workflow for brain radiotherapy, that eliminates the registration uncertainty through calculation of a synthetic CT (sCT) from MRI data.

**Methods:**

A total of 54 patients with an indication for radiation treatment of the brain and stereotactic mask immobilization will be recruited. All study patients will receive standard therapy and imaging including both CT and MRI. All patients will receive dedicated RT-MRI scans in treatment position. An sCT will be reconstructed from an acquired MRI DIXON-sequence using a commercially available deep learning solution on which subsequent radiotherapy planning will be performed. Through multiple quality assurance (QA) measures and reviews during the course of the study, the feasibility of an MRI-only workflow and comparative parameters between sCT and standard CT workflow will be investigated holistically. These QA measures include feasibility and quality of image guidance (IGRT) at the linear accelerator using sCT derived digitally reconstructed radiographs in addition to potential dosimetric deviations between the CT and sCT plan. The aim of this clinical study is to establish a brain MRI-only workflow as well as to identify risks and QA mechanisms to ensure a safe integration of deep learning-based sCT into radiotherapy planning and delivery.

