### Statistical design

To estimate the required patient number, the MRI images of all brain stereotactic treatments at the stereotactic linear accelerator of our center, who received a dedicated RT simulation MRI from the last 3 years were examined retrospectively for artifacts and other exclusion criteria of an sCT workflow. The results showed that 91% of the 45 patients would have been suitable for an sCT workflow. 5% of patients were not suitable due to claustrophobia. A further 4% of patients were not eligible because they had metal artifacts on the skull due to surgery or had a glass eye, for example. According to Masitho et al. [25], further exclusion based on dose deviations in OARs or PTVs in comparison to the planning CT are not to be expected. Only one patient was found to have problems with sCT reconstruction. Thus, the overall feasibility of sCTs workflows is estimated to be 90%.

The case number calculation for the study is based on a one-stage design for pilot studies by Fleming [32]. The calculation is based on the following general conditions:

According to the information of the retrospective analysis of all stereotactic brain patients in the past three years, the application of the sCT workflow is considered feasible if the study procedure described above proves to be feasible accordingly. It is expected and postulated for a positive evaluation of the study outcome that this is the case in 90% of patients.The sCT workflow, on the other hand, would be considered not sufficiently feasible if the feasibility rate was 75% or less.The probability of erroneously assessing the experimental intervention as feasible even though the true feasibility is at/below 75% (α-error) is said to be only 5%.The probability of erroneously discarding the experimental measure as not sufficiently feasible although the true feasibility rate is 90% or more (β-error) should be no more than 10%, corresponding to a power of the study of 90%.

According to these parameters *n* = 54 patients who can be evaluated in terms of feasibility are needed.

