Patients who show a violation of the inclusion criteria at the time of inclusion in the study (“non-eligible”) are excluded from the statistical analysis (e.g. Unsuitable for MRI due to metallic implants, withdrawal of consent, immobilization without stereotactic mask). These cases will only be reported casuistically. Which patients with serious protocol violations fall into this category is decided prospectively in a “blind review” before the analyses are carried out.

All other patients are included in the evaluation of the primary objective criterion in the sense of an “intention-to-treat analysis” (ITT).

The primary study objective criterion is calculated by dividing the number of ITT patients in whom the experimental method was found to be feasible by the total number of ITT patients. The exact one-sided 95% and 90% confidence intervals are calculated for the resulting rate.

The analysis of all other parameters is done descriptively, depending on the data type, with frequencies, means, medians, ranges of values and/or confidence intervals, if applicable.

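### 54 is given both as the number recruited and as the evaluable number needed, with no reserve for the patients the analysis rule drops

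*Protocol article*

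**What the plan says.** The Methods paragraph of the abstract gives the recruitment total: "A total of 54 patients with an indication for radiation treatment of the brain and stereotactic mask immobilization will be recruited". The Statistical design section arrives at the same number for a different quantity: "54 patients who can be evaluated in terms of feasibility are needed".

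That section rests the number on a one-stage Fleming design. The workflow "would be considered not sufficiently feasible if the feasibility rate was 75% or less", the expected rate is 90%, the α-error is 5% and the power is 90%.

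It then defines the analysis set. Patients who violate the inclusion criteria at the time of inclusion "are excluded from the statistical analysis" and are only described case by case. The examples are unsuitability for MRI because of metallic implants, withdrawal of consent, and immobilization without the stereotactic mask. A blind review before the analysis decides which serious protocol violations belong to this group. Everyone else stays in the denominator as the ITT set. For the primary rate, "The exact one-sided 95% and 90% confidence intervals are calculated for the resulting rate".

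The article states neither an allowance for excluded patients nor a replacement rule.

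**The concern.** The same figure is used for two quantities that the analysis rule separates. If 54 are recruited and one is later classed as non-eligible, 53 are evaluable and the requirement in the Statistical design section is not met. The plan foresees such cases, since it sets out how they are identified and reported.

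Two things depend on the evaluable number. One is the stated power. The other is the number of successes needed for a positive result, which changes with the denominator. If the article does not say which of the two numbers is 54, it is unclear when recruitment stops and which threshold then applies.

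**Working it through.** **Inputs** (all from the Statistical design section): p0 = 0.75, p1 = 0.90, one-sided α = 0.05, power 0.90. The one-sided reading follows from the one-sided intervals planned for the primary rate. The number of exclusions is not given, so I assume 0 to 6, that is n = 54 down to 48.

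**Step 1. Reproduce the 54.** One-sample normal approximation:

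n = [(z₀.₉₅·√(p0(1−p0)) + z₀.₉₀·√(p1(1−p1))) / (p1−p0)]²
= [(1.645 × 0.4330 + 1.282 × 0.3000) / 0.15]²
= 53.46, rounded up to 54.

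The figure reproduces, and it is the bare evaluable number. Nothing has been added for exclusions.

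**Step 2. Power by the same approximation when patients are lost.** Power = Φ[((p1−p0)√n − 1.645 × 0.4330) / 0.3000]. For n = 54: (0.15 × 7.348 − 0.7122)/0.3 = 1.300, so 90.3%. For n = 53: (0.15 × 7.280 − 0.7122)/0.3 = 1.266, so 89.7%. The other values follow in the same way.

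**Step 3. Exact one-sided 5% test.** A positive result is the smallest r with P(X ≥ r | n, 0.75) ≤ 0.05. This is the same as the exact one-sided 95% interval lying above 75%. Power is P(X ≥ r | n, 0.90).

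| Evaluable n | Normal-approximation power | Exact cut-off r | Exact α | Exact power |
|---|---|---|---|---|
| 54 | 90.3% | 47 | 2.41% | 83.2% |
| 53 | 89.7% | 46 | 2.83% | 84.4% |
| 52 | 89.1% | 45 | 3.32% | 85.6% |
| 51 | 88.4% | 44 | 3.88% | 86.7% |
| 50 | 87.7% | 43 | 4.53% | 87.8% |
| 49 | 87.0% | 43 | 2.30% | 78.5% |
| 48 | 86.2% | 42 | 2.72% | 80.0% |

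**Reading the table.** On the basis that yields the plan's 54, the first unreplaced exclusion takes power just below 90%, and six exclusions cost about 4 percentage points (90.3 − 86.2 = 4.1). On the exact test, power moves in steps because the cut-off is a whole number. It rises with one to four exclusions and is below the n = 54 value only at five or six. At n = 54 a cut-off of 46 would give 91.4% power, but with an α of 5.25%, above the stated 5%.

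**The case against.** The strongest reply is that this is a matter of wording. The governing sentence in the Statistical design section does say evaluable; only the abstract says recruited. The article condenses a full protocol that is not shown, and that protocol may replace excluded patients. The exclusion rule is also narrow: it concerns violations present at inclusion, and withdrawal of consent appears only as an example within that group. A patient who fails a verification and moves to the CT-based workflow stays in the denominator as a failure and does not reduce the evaluable number.

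Much of this stands. A shortfall is not certain, because it needs at least one exclusion and no replacement, and no rate is given. But a replacement rule in the full protocol would mean that more than 54 are recruited whenever it is used, so the abstract's total would still need correcting.

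Two stronger readings are tempting and are not supported.

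- A reader might infer that exclusions are what take the trial below 90% power on the exact test. They are not: n = 54 itself reaches only 83.2%, and n = 50 to 53 all do better.
- A reader might take the retrospective shares of 5% (claustrophobia) and 4% (metal artifacts or a glass eye) as a loss rate of 5% to 9% and conclude that 57 to 60 recruits are needed (54/0.95 = 56.8; 54/0.91 = 59.3). Those shares are the unsuitable cases that bring the retrospective figure down to 91% and so feed the 90% feasibility assumption. Using them again as attrition counts them twice. Claustrophobia is not among the listed reasons for exclusion, and metal that contraindicates MRI is already an exclusion criterion at entry.

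**Conclusion.** The point holds as an inconsistency in the stated sample size. Recruiting 54 secures 54 evaluable patients only with no exclusions or with replacement; the article foresees exclusions and states no replacement, and the calculation contains no reserve. The consequence is modest: on the plan's own approximation, less than one percentage point of power for the first patient lost and about four for six.

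The exact-test figures assume that the positive decision is taken at one-sided 5%, matching the stated α and the 95% interval. On that assumption the distance to 90% is a separate matter that exists before any exclusion. It bears on the correction only in this way: securing 54 evaluable patients restores the stated number but does not by itself deliver 90% exact power. The point is worth correcting and does not threaten the trial.

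**What to change.** State the recruited and the evaluable number separately, in one of two ways.

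1. Set the target as 54 evaluable patients, with each patient excluded as non-eligible replaced, and change the abstract to match.
2. Keep 54 as the number recruited, say that the evaluable number may be lower, and give the exact cut-off and power for each plausible evaluable number, including 54. The table above supplies these for 48 to 54.

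Under either option, give the exact power at 54 (83.2% with a cut-off of 47) so that the reader does not take 90% as the exact figure. It would also help to say whether withdrawal of consent after inclusion leads to exclusion or counts as a failure, since that decides how many replacements could arise.

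The cost is a sentence or a short table. Under the first option it is also one further patient per exclusion; the article gives no basis for predicting how many.

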**Discussion:**

Compared to CT, MRI offers a superior soft tissue contrast without additional radiation dose to the patients. However, up to now, even though the dosimetrical equivalence of CT and sCT has been shown in several retrospective studies, MRI-only workflows have still not been widely adopted. The present study aims to determine feasibility and safety of deep learning-based MRI-only radiotherapy in a holistic manner incorporating the whole radiotherapy workflow.

**Trial registration:**

NCT06106997.

## Background

Radiotherapy (RT) is an important treatment modality for patients with malignant diseases of the brain such as primary brain tumors and metastases. A further improvement in the local effectiveness of (stereotactic) radiotherapy is likely beneficial for the quality of life and also prognosis of patients receiving RT. Traditionally computed tomography (CT) images are used for planning while magnetic resonance imaging (MRI) images are used for tumor delineation. Therefore, they need to be registered, which is an error prone process [1, 2]. One approach to avoid the registration uncertainty between MRI and CT is the so-called MRI-only workflow, where synthetic CT images are calculated from the MRI data.

Treatment planning relies on high-resolution CT imaging data, which can be transformed into an electron density distribution to model the interaction of the high-energy treatment beam and the human tissue. In conventional RT treatment planning, CT images have been the primary basis of radiotherapy treatment planning and delivery.

CT scans lack sufficient soft tissue contrast in the brain, making it challenging to achieve adequate segmentation of tumor volumes and organs-at-risk (OARs), such as the optic chiasm, and brainstem. Optimization of treatment parameters and evaluation of dose distribution require high resolution and high contrast imaging for target volume definition. Therefore, especially in stereotactic treatments, where high single doses are applied with high precision in one (stereotactic radiosurgery) or a few (fractionated stereotactic radiotherapy) treatment sessions, an MRI scan is essential. The MRI scan typically consists of multiple sequences and provides sufficient soft tissue contrast to differentiate the target volume from healthy brain tissue.

Currently, to incorporate the segmented volumes into the radiation treatment planning, a rigid registration of the CT- and MRI-image is performed. Based on the registration parameters the segmented structures are propagated onto the CT scan. This registration process is subject to uncertainties, which are quantified to be approximately  2 mm [1] and affect all treatment fractions of the patient systematically. Therefore, the registration uncertainty must be considered in the safety margins around the clinical target volume (CTV), resulting in a correspondingly larger planning target volume (PTV). Meanwhile, the typical safety margin from the CTV to the PTV is in the order of only 1–2 mm. Due to these steep gradients, even small deviations can lead to damage of healthy tissue and marginal miss. Therefore, a high degree of accuracy is required throughout the planning process [3–5].

The uncertainties in registration between CT and MRI can be avoided by adopting a solely MRI-based approach, known as the MRI-only workflow. To eliminate the CT from the RT planning process, synthetic CT images (sCT) must be computed from the MRI data to obtain the Hounsfield Units (HU) or electron density information. Besides avoiding registration associated risk of systematic deviations the MRI-only workflow saves time, since patients only need to be scheduled on one imaging modality. Moreover, radiation in the order of few millisieverts of dose from the additional CT examination can be avoided. The reduced registration uncertainty also leads to nominally reduced CTV-PTV safety margins [6].

To compute the sCT from MRI-images different algorithms have been developed over time. The techniques for sCT calculation [7] include bulk-density approaches [8, 9], Atlas- [10, 11], Voxel- [12, 13] and deep learning-based [14, 15] algorithms. Early approaches used a combination of multiple dedicated MRI sequences, such as DIXON, and UTE sequences to distinguish fat, muscle, bone and air [16–20], leading to total acquisition times of around 12–15 min [21], as they required multiple dedicated MRI sequences. In recent years, artificial intelligence-based algorithms have been successfully developed [16, 17, 22]. Unlike voxel, atlas, or bulk-density-based approaches, these algorithms often require only a single sequence. Short DIXON sequences (3:25 min [22, 23]) serve as a basis for these algorithms, which are also part of clinical standards in routine imaging [22]. Dosimetrically, the sCT reconstructed via artificial intelligence approaches matches very well with CT-based clinical standards, with deviations < 1% of the PTV dose [16, 17, 22].

In addition to dose calculation, the sCT must also be suitable for patient positioning and verification. Therefore, MRI scans must be performed with the patient immobilized using a thermoplastic mask in the treatment position. However, this is often not possible in the diagnostic setup because the mask is not compatible with the head receiver coils used in diagnostics. Additionally, MRI-compatible immobilization aids, such as mask holders, are needed as the carbon-fiber-made holders used in radiotherapy are not MRI-compatible. Many medical device manufacturers offer MRI-compatible products for various mask systems, allowing scans in the mask and treatment positions to be performed with flexible coils, leading to sufficiently good images [17, 22] and fewer motion artifacts due to immobilization [24].

After the approval and verification of the radiation treatment plan, the actual radiation treatment is performed. In each treatment session, the patient, immobilized by a mask, must be precisely aligned with the treatment beam as specified in the imaging and treatment planning process. The adjustment of the patient’s position and rotation is based on rigid correction parameters of the treatment table parameters calculated on kV imaging at the medical linear accelerator, where cone-beam CT (CBCT) or 2D/2D X-ray images are created in the treatment position and registered with the CT scan underlying the treatment plan.

It was shown that sCTs can also serve as a reference for CBCT positioning systems, with differences < 1 mm/° compared to CT as the clinical standard [25], whereas deviations in mask alignment and mask holder can reach up to 3 mm/° at maximum [26]. For radiation therapy in the head region, 2D/2D X-ray systems offer a strong correlation between the brain and the skull bones. They are often used because compared to CBCT they are significantly faster, allow for additional checks after table rotation, and require less imaging dose. MRI-only workflows are also possible for such systems, as demonstrated by Masitho et al. [22].

The implementation of MRI-only workflows should ideally consider the mask holder and the mask itself in the dose calculation, even though they have minimal influence on the dose distribution. For stereotactic prescription concepts with 80% of the reference dose, the homogeneity of the dose distribution in the target volume is secondary, and small deviations caused by the (unmodeled) mask should not have a clinical impact. Since these materials are invisible in MRI and often differ between the MRI and CT versions of the mask holder, calculating the mask system as part of sCT creation is challenging. To account for these materials in the sCT, Masitho et al. [27] proposed the use of MRI-visible silicone rods built into the MRI-compatible mask holder, which serve as the basis for creating a model of the mask holder as HU distribution in the planning system. The mask itself is modeled by expanding the patient-air interface. Masitho et al. showed that with this approach, dose differences of 0.2 ± 1.03% can be achieved in the PTV [27]. Taking into account the absolute dosimetry uncertainty, the dosimetric significance is 2% for ΔD50 and ΔD0.01ccm for PTV and OAR [28, 29].

Despite the studies mentioned above, MRI-only workflows are still not widely adopted. This might be due to the limited availability of MRI scanners in radiotherapy clinics or departments. One other explanation could be that the implementation in daily practice is too complex, leading to a lack of acceptance for such workflows. The commercially available sCT software used in this study (CE-labeled sCT algorithm of syngo.via RT Image Suite (VB60) by Siemens Healthineers GmbH) was evaluated for its accuracy in a retrospective research context with 26 patients [2, 27]. Still, proof of feasibility is missing to establish an MRI-only workflow since the whole treatment process of the patient has to be evaluated.

Therefore, this study will prospectively investigate whether an MRI-only workflow is feasible for the stereotactic treatment of patients with brain lesions. In order to enable a smooth integration of the sCT into the clinical routine, the entire radiotherapy chain must be able to be carried out with the help of the sCT. For this purpose, the patients have to be imaged in a radiotherapy mask in the MRI to ensure the same position of the patients in imaging and radiation. Secondly, a dosimetric equivalence of sCT and CT must be assured to enable dosimetrically correct radiation planning for the patients. In addition, mask holder and the mask itself must be correctly integrated into the sCT, as these structures are not visible in the MRI. Furthermore, the patient must be reliably positioned on the treatment couch at each fraction. For this purpose, it must be possible to rely on digitally reconstructed radiography (DRR) from the sCT in order to check the positioning with the help of non-coplanar X-ray images. During the course of this study these parameters are assessed to examine the feasibility of an MRI-only workflow and to identify potential difficulties and exclusion criteria for patients or treatment indications.

## Methods

### Study design

This study is an open, mono-centric, non-randomized, prospective study to evaluate feasibility of an MRI-only workflow providing accurate treatment planning and patient positioning. Patients eligible for the sCT-Feasibility trial require an indication for brain radiotherapy in either the definitive or postoperative setting and must have no MRI contraindications.

Each participant of the study will undergo the standard of care imaging for treatment planning, consisting of both MRI and CT scans, each performed within five days before the commencement of treatment. However, within the study the treatment will be based on MRI-only, i.e. treatment planning and positioning of the patients with 2D/2D imaging at the linear accelerator will be based on synthetic CT data. Feasibility of such a workflow will be evaluated en route by verification against the standard treatment as schematically outlined in Fig. 1 and described in detail in Sect. 2.4.

**Fig. 1 Fig1:**
[figure not shown]
Schematic depiction showing imaging, treatment planning, and radiotherapy of study patients. Each participant of the study will receive MRI and CT scans, as in the standard CT-workflow. The sCT workflow differs only in terms of the data used for treatment planning. The precision and feasibility of the sCT-based process are assessed at various stages during treatment, and if significant deviations occur, the treatment is continued using the conventional clinical standard

